## Discussion

Despite the frequent occurrence of distal radius fractures, treatment is still at debate. The ultimate goal of treating a distal radius fracture is to restore full wrist function as early as possible. Full range of motion in the wrist declines with disuse and the introduction of early motion following a fracture is critical for the early restoration of normal function, but also for regaining ADL independence. Especially the latter is considered the main strength of the IlluminOss® System. The IO-Wrist study is aimed at determining the effect of operative treatment of distal radius fractures using the IlluminOss® System. Treating patients with this device is expected to result in good and fast functional recovery (i.e., low DASH and high PRWE scores). When comparing outcome with published data on non-operative treatment (i.e., closed reduction and 4–6 weeks plaster cast immobilization, with surgical intervention only if secondary dislocation occurs), we expect similar outcome at 1 year post-injury. However, improved DASH scores are expected to be noticeable until 6 months after treatment initiation, reflecting faster functional recovery in the operative group. Patients operated with IlluminOss® are expected to regain independence sooner and therefore to consume less health care. Improved recovery as well as less total health care use would justify higher costs for the initial surgery. As far as we know, this is the first high-quality study that will evaluate outcome after treating patients with an extra-articular distal radius fracture operated with the IlluminOss® System, using patient-reported, clinical, and economic outcomes.

Four hospitals in the Netherlands participate in this study. The first patient was included on August 31, 2015. Inclusion is expected to be completed within a year. With a follow-up of 1 year data presentation is expected by the end of 2017.

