The llluminOss® System is the first percutaneous, patient-specific, fracture stabilization system [16]. Only a small and percutaneous incision is required to insert an inflatable balloon into the medullary canal. The balloon, which spans the fracture is infused with a light curable monomer. The monomer hardens in situ by applying a visible light, resulting in a stable and patient-specific implant that provides longitudinal strength and rotational stability over the length of the implant. Early functional after-treatment without additional plaster immobilization is possible. The latter is considered the main strength of this device over non-operative treatment and conventional metal implants [16].

The IO-WRIST study is designed to determine results after treatment with IlluminOss®. Outcome will be monitored as propagated by the distal radius working groups of the International Society for Fracture Repair and the International Osteoporosis Foundation [17]. This study primarily aims to examine the effect of operative treatment using the IlluminOss® System on the DASH (Disabilities of the Arm, Shoulder, and Hand) score in elderly patients who sustained a unilateral, displaced, extra-articular distal radius fracture. Secondary objectives are to examine the effect on functional outcome, the level of pain, health-related quality of life, the time to regaining independence in activities of daily living (ADL), the resumption of work/ADL, range of motion of the wrist, the time to radiographic healing, the rate of complications with associated secondary interventions, and the costs for health care use and lost productivity.

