### Outcome measures

The primary outcome measure is the Disabilities of the Arm, Shoulder and Hand outcome measure (DASH). This questionnaire is validated and is completed by patients. It reflects the disability experienced by patients with an upper-limb disorder, and is used for monitoring changes in symptoms and function over time [19–22]. The DASH disability/symptom score is the sum of responses to 30 items (scored 1-5), which test a) the degree of difficulty in performing a variety of physical activities (21 items); b) the severity of pain, activity-related pain, tingling, weakness, and stiffness (5 items); and c) the effect on social activities, work, sleep, and self-image (4 items). The total score ranges from zero (no disability) to 100 points (severe disability). At least 27 of the 30 items must be completed. A validated Dutch version is available [23]. The DASH optional modules for Work and high performance Sport/Music (both 4 items, scored 1–5) will also be completed. The score can only be calculated if all items are completed.

The secondary outcome measures are:Patient-Rated Wrist Evaluation (PRWE)Pain level at both sides (VAS)Health-related quality of life: Short Form-36 (SF-36) and EuroQoL-5D (EQ-5D)Time to regaining independence in Activities of Daily Living (ADL)Resumption of work and other activities of daily livingRange of Motion of the wrist at both sidesRadiographic evaluationComplicationsSecondary interventionsHealth care consumption with associated costsProductivity loss with associated costs

The Patient-Rated Wrist Evaluation (PRWE) measures functional outcome in patients diagnosed with a distal radius fracture [24]. In this 15-item questionnaire, patients are asked to rate the level of pain and disability in their wrist from zero (no pain/difficulty) to 10 (worst pain/unable to do) [25, 26]. The PRWE consists of a 5-item Pain subscale, a 6-item Specific Activities subscale, and a 4-item Usual Activities subscale. Responses to the individual subscales are summed. The total score for wrist pain and disability (100 points) is computed by dividing the sum of the ten functional items by two and adding that subtotal (50 points) to the score for the pain subscale (50 points). This provides a score that ranges from 0 (no pain or disability) to 100 (high level of pain or disability). A validated Dutch version is available [27].

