### Study procedures

Patients will be followed for 1 year. Follow-up visits are scheduled at 2 weeks, 6 weeks, 3 months, 6 months, and 12 months after index surgery. These visits are standard of care for patients with a distal radius fracture. Table 1 shows an overview of the follow-up schedule, including the accepted windows around each visit.

**Table 1 Tab1:** Schedule of events

Radiographs & Events	Screening	Enrolment	Baseline	Per/Post	2 weeks	6 weeks	3 months	6 months	12 months
				surgery	(10–16 days)	(5–7 weeks)	(11–15 weeks)	(5–7 months)	(12–14 months)
X-Ray^a^	X				(optional)	X	X	X	(optional)
Screening	X								
Informed Consent		X							
Baseline Data			X						
Surgical Report Form				X					
Clinic FU					X	X	X	X	X
Range of Motion					X	X	X	X	X
DASH					X	X	X	X	X
PRWE					X	X	X	X	X
Pain (VAS)					X	X	X	X	X
SF-36					X	X	X	X	X
EQ-5D					X	X	X	X	X
ADL independence					X	X	X	X	X
Work/ADL resumption					X	X	X	X	X
Complications					X	X	X	X	X
Secondary Interventions					X	X	X	X	X
Health Care Use					X	X	X	X	X
Early Withdrawal					^b^	^b^	^b^	^b^	^b^

^a^The AP and lateral X-rays will be used for determining radiographic healing

^b^Only applicable at time of withdrawal

During these regular clinical follow-up visits, AP and lateral radiographs are made for determining radiographic healing and malalignment.

At each planned visit, the clinical investigator (or a research assistant) will document complications and secondary interventions, and will check information within the patients’ hospital files. At the last visit, all planned secondary interventions will also be recorded.

At each planned visit, a physician, clinical investigator, or research assistant will measure the range of motion of the wrist using a goniometer. In addition, patients will be requested to complete a set of questionnaires (DASH, PRWE, VAS for pain, SF-36, EQ-5D, ADL/work, health care consumption, and production loss).

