### Sample size calculation

For case series, a generally accepted assumption is that introducing and implementing a (relatively new) surgical technique requires 30 patients [39]. A formal sample size calculation for this study is based on the DASH score (primary outcome measure). The minimal important change for the DASH score is 10 points [19]. Based on literature data we expect a mean DASH of 23 (SD 19) in non-operatively treated patients [40, 41]. In order to detect a 10-point improvement (mean 13, SD 10) in patients treated with IlluminOss® with a two-sided α of 0.05 and a 90 % power (β = 0.10), at least 38 patients are needed. Anticipating 10–15 % loss to FU and 10 % mortality, 50 patients will be enrolled.

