### Statistical analysis

The Statistical Package for the Social Sciences (SPSS) version 21 or higher (SPSS, Chicago, Ill., USA) will be used for statistical analysis. The STrengthening the Reporting of OBservational studies in Epidemiology (STROBE) guidelines will apply to data reporting. If necessary, missing values will be replaced using multiple imputation following the predictive mean matching method, using ten imputations. The Shapiro-Wilk test will be used for testing normality of continuous data. All statistical tests will be two-sided, and a p-value <0.05 will be used as threshold of statistical significance.

Descriptive analysis will be performed in order to report baseline and outcome data. Data will be reported as mean with SD (continuous, parametric data), as median with first and third quartile (continuous, non-parametric data), or as number with frequency (categorical data). A Wilcoxon Signed Rank test will be applied for comparing continuous outcome scores at 1 year with those at their first measurement.

Depending on the variability of covariates, multivariable analysis may be performed. A linear mixed-effects regression model will be made to model the relation between specific covariates and the outcome measures that are recorded repeatedly (i.e., DASH and other PROMs). This multilevel model will include fixed effects for covariates like involvement of the dominant side, gender, and age if deemed necessary. These confounders will be selected based upon literature data and by eyeballing the descriptive statistics. The beta values will be reported with their 95 % confidence interval and p-value. Estimated marginal mean will be computed and reported per follow up moment.

For the continuous data determined only once (e.g., time to radiographic healing), a multivariable linear regression model may be developed, with the outcome measure as dependent variable. Potentially confounding variables will be entered as covariate. Beta values will be reported with 95 % confidence interval and p-value.

For the categorical data, a multivariable logistic regression model will be developed, with the outcome measure as dependent variable. Potentially confounding variables will be entered as covariate. Odds ratio’s will be reported with 95 % confidence interval and p-value.

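### The 10-point DASH gain behind the sample size has no time point, cannot lie at 1 year on the plan's own expectation, and is compared with its benchmark in no named analysis

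*Protocol article*

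**What the plan says.** All references are to the protocol article.

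- **Background (objective):** "This study primarily aims to examine the effect of operative treatment using the IlluminOss® System on the DASH" score. No time point is attached. The Outcome measures section names DASH as primary, also without one.
- **Sample size calculation:** "The minimal important change for the DASH score is 10 points", and "we expect a mean DASH of 23 (SD 19) in non-operatively treated patients". The target is a 10-point improvement to a mean of 13 (SD 10), with two-sided α 0.05 and 90 % power. This gives 38 patients, raised to 50 for loss to follow-up and mortality. No visit is given for 23 or for 13.
- **Study procedures:** "Follow-up visits are scheduled at 2 weeks, 6 weeks, 3 months, 6 months, and 12 months after index surgery". Table 1 schedules DASH at all five.
- **Statistical analysis:** a Wilcoxon signed rank test is planned for "comparing continuous outcome scores at 1 year with those at their first measurement". A mixed model yields an estimated marginal mean at each follow-up. No comparison with 23 is described.
- **Discussion:** against published non-operative results, "we expect similar outcome at 1 year post-injury", whereas "improved DASH scores are expected to be noticeable until 6 months after treatment initiation".
- **Study population:** fixation may take place up to 14 days after trauma.

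**The concern.** A DASH mean has a meaning only at a stated time in recovery. The sample size section gives the benchmark, target, both SDs, α, power and number of patients, but not the time to which 23 and 13 refer. The Discussion then excludes the last visit as the place where a gain over non-operative care is expected.

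Two things are at stake. With five sets of DASH scores and no named visit, the headline can be chosen after the data are seen. And the only test over time that the plan names asks whether patients improved after their first measurement. A significant result there could be reported as success of the primary aim although it says nothing about the 10-point gain for which the study was sized.

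**Working it through.** **1. Which comparison lies behind 38?** Inputs from Sample size calculation: difference 23 − 13 = 10; SD 19 (non-operative) or 10 (IlluminOss®); two-sided α 0.05; power 90 %.

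One sample against a fixed mean, normal approximation: n = (z0.975 + z0.90)² × SD² / difference².

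- (1.960 + 1.2816)² = 10.507
- SD 19: 10.507 × 361 / 100 = 37.93, rounded up to **38**, the stated figure
- SD 10: 10.507 × 100 / 100 = 10.51, rounded up to 11
- Two arms with SDs 19 and 10: 10.507 × (361 + 100) / 100 = 48.44, or 49 per arm

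Only the first matches. Enrolment also matches: 38 / (0.85 × 0.90) = 49.7, rounded up to 50. The arithmetic is sound, and it shows that the study was sized for a comparison with a fixed value of 23.

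**2. At which visit can the gain lie?**

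| Visit after surgery | Gain over non-operative care expected in the Discussion? | Named comparison with 23? |
|---|---|---|
| 2 weeks | within the expected window | none |
| 6 weeks | within the expected window | none |
| 3 months | within the expected window | none |
| 6 months | end of the expected window | none |
| 12 months | no, similar outcome expected | none |

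Four visits remain possible, and the article does not choose among them.

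**3. Does the named test examine the powered gain?** The Wilcoxon test compares each patient's 1-year score with that patient's first score, scheduled at 2 weeks. Its null hypothesis is no change since then. The powered null hypothesis is a mean of 23. Normal recovery can make the first false while the second is true, so the test can be significant with no gain over non-operative care.

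**4. Why the visit matters for power.** For 38 patients in the one-sample comparison of step 1 (normal approximation), power depends on the true gain at the chosen visit. The gains of 5 and 2 are assumptions, used to show a range.

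| True gain | SD 19 | SD 10 |
|---|---|---|
| 10 | 90 % | above 99 % |
| 5 | 37 % | 87 % |
| 2 | 10 % | 23 % |

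The plan's 90 % therefore holds only at a visit where the gain is as large as 10 points.

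**5. Time origin.** Visits count from surgery, 0 to 14 days after injury. In adjacent sentences the Discussion counts once from injury and once from the start of treatment. The largest offset relative to nominal visit time is 14/14 = 100 % at 2 weeks, 14/42 = 33 % at 6 weeks and 14/365 = 4 % at 1 year. With the accepted window of 5–7 weeks, a 6-week visit can fall as late as 7 + 2 = 9 weeks after injury.

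**The case against.** The best defence is that this is a case series with mainly descriptive reporting, also justified by a 30-patient convention, and that a journal article condenses its protocol. The 10 points may simply be meant for the period up to 6 months, in which case the two sections do not conflict. DASH is also estimated at every visit through the marginal means.

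Part of this stands. No sentence claims a 10-point gain at 1 year, so the fault is an unstated time point, not two flatly opposed statements. But the article chose to give a formal power claim and foresees comparison with published non-operative results. The missing visit is what gives 23 and 13 their meaning, and estimating all five means does not say which one answers the primary question.

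Three stronger readings are tempting, and the article does not support them.

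- **That 1 year is the only time point tested, so the study tests where it expects nothing.** The Wilcoxon test is a within-patient contrast of two times. Similar 1-year results to non-operative care are compatible with a large change in it.
- **That power at 1 year is 5 % instead of 90 %.** This would describe a test against 23 at 1 year, which the plan does not name. Power equals α at zero effect for any test.
- **That the benchmark runs from injury, so early comparisons favour the device by several points.** The article gives no time origin for the published 23. Any shift in points needs an assumed rate of recovery and an actual delay, and only the 0 to 14 day limit is stated. The mixed origins are real, but their effect on DASH is unknown in size and direction.

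**Conclusion.** The point holds for the undefined time point and the missing matching analysis. The primary outcome, the benchmark of 23 and the 10-point gain have no visit. On the plan's own expectation the gain is not at 1 year, so it belongs to one of four unnamed earlier visits. The comparison for which 38 patients were calculated is specified at none of them, and the named test over time answers a different question. Following the article as written leaves the 90 % power attached to no analysis and the headline visit open to choice among five.

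This rests on reading the 38 as a one-sample calculation, which the exact match supports, and on taking the Discussion's expectation at face value. The calculations of 38 and 50 are not in error. The time-origin issue is secondary: negligible at 1 year, possibly relevant at 2 and 6 weeks, and not quantifiable in DASH points from the article.

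**What to change.** 1. Name one primary DASH visit within the window up to 6 months where benefit is expected, and fix it before outcome data are examined.
2. State the time point and time origin of the benchmark of 23 (SD 19). If it does not belong to the chosen visit, replace it with published non-operative data that do.
3. Make the primary analysis the mean DASH at that visit with its 95 % confidence interval, taken from the marginal means already planned, set against that benchmark. The other visits and the Wilcoxon test become secondary, with the Wilcoxon result described as recovery since the first measurement.
4. If the benchmark mean or SD changes, recalculate and restate the power for the 50 enrolled (50 × 0.85 × 0.90 = 38.25 expected to be evaluable), without enrolling more.
5. For early benchmark comparisons, also report time since injury, using the injury-to-surgery interval already collected.

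The cost is an amendment to the text and a search for a benchmark at the right time. No new data are needed. The downside is that the benchmark and the stated power may have to be revised, and the power may turn out lower than 90 %.

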## Abbreviations

ADL: activities of daily living
AO: arbeitsgemeinschaft für osteosynthesefragen (German for “Association for the Study of Internal Fixation”)
AP: anteroposterior
ASA: American Society of Anesthesiologists
BP: bodily pain
DASH: disabilities of the arm, shoulder and hand score
ED: emergency department
EQ-5D: euroQol-5D
GH: general health perception
MCS: mental component summary
MH: general mental health
MREC: Medical Research Ethics Committee
NTR: Netherlands Trial Registry (in Dutch: Nederlands Trial Register)
OTA: Orthopaedic Trauma Association
PACS: picture archiving and communication system
PCS: physical component summary
PET: polyethylene terephthalate
PF: physical functioning
PROMs: patient-reported outcome measures
PRWE: patient-rated wrist evaluation
QoL: quality of life
RE: role limitations due to emotional problems
ROM: range of motion
RP: role limitations due to physical health
SD: standard deviation
SF: social functioning
SF-36: short form-36
SPSS: statistical package for the social sciences
STROBE: strengthening the reporting of observational studies in epidemiology guidelines
VAS: visual analog scale
VT: vitality, energy, or fatigue
WMO: medical research involving human subjects act (in Dutch: Wet Medisch-wetenschappelijk Onderzoek met Mensen)
